The MHRN risk model development and validation studies demonstrated accuracy but did not evaluate whether the models increase identification (screening) and recognition (risk assessment) or result in patients receiving more suicide prevention services (treatment) and fewer crisis services or making fewer suicide attempts. The current study is designed to answer these important implementation questions and to understand factors that could support rapid scale-up and widespread use should the risk model prove effective. This study combines the MHRN suicide risk identification model (to flag patients estimated to be at risk for suicide) and the ZS framework (to identify, engage, and treat patients identified at risk for suicide) in an innovative approach across three integrated health care systems’ behavioral health clinics to increase the reach and effectiveness of suicide prevention care models.

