## Methods

### Objectives and hypotheses

The current study will test the implementation of the MHRN suicide risk model in behavioral health clinics to facilitate identification, recognition, and engagement in supportive suicide prevention services among individuals estimated to be at risk for suicide. The study’s main aim is to examine the effectiveness of a suicide risk model on fatal and non-fatal suicide attempts (primary outcome). The secondary outcome analyses examine the following questions: Are patients who receive care in the behavioral health intervention clinics more likely to be referred to and receive supportive outpatient behavioral health services than patients in usual care clinics? Are they more likely to receive supportive services sooner after risk recognition than they would have before the risk models were used, or earlier than patients in usual care clinics? Are they less likely to require crisis services and less likely to attempt suicide? Specifically, we will test the hypothesis that the risk model will lead to a reduction in suicide attempts (primary outcome) and an increase in referrals to, and receipt of, supportive outpatient services (secondary outcome).

In secondary analyses, we will determine whether implementing a suicide risk model into a suicide prevention care model improves identification of patients at risk for suicide attempt (suicide screening practices); that is, whether the enhanced identification using a risk model improves upon self-reported risk screening relied upon in usual care. Specifically, does the risk model (intervention) identify additional patients for screening who would not be identified in the course of usual care? How many additional patients are recognized (complete a risk assessment)? We hypothesize that the risk model may identify people who miss or refuse screening, deny risk because they do not believe themselves to be at risk or feel ambivalent, or deliberately conceal their risk. We will test the hypothesis that the suicide risk model implementation will improve identification and recognition of patients at increased risk of suicide attempt compared to usual care.

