### Proposed care models (mechanisms of action)

Figure 3 shows a standard suicide prevention care model (usual care) and the proposed enhanced care suicide risk model (intervention). A typical workflow that involves suicide risk identification, when a patient presents for a behavioral health visit, may begin with suicide risk screening (typically the PHQ9 [42] in the participating sites). If the PHQ9 is missed, refused, or if item 9 (“Over the last two weeks, how often have you been bothered by thoughts that you would be better off dead or of hurting yourself in some way?”) is denied, the workflow may terminate, however a clinician could also proceed if clinically indicated. Potentially terminal processes are indicated by a dark background in Fig. 3, text boxes with white backgrounds indicate continuation of the workflow. The expectation is that when patients respond positively to item 9 (i.e., respond with a score of 2 “more than half the days” or 3 “nearly every day”), a comprehensive suicide risk assessment is conducted (typically the Columbia Suicide Severity Rating Scale [C-SSRS] [43] in the participating sites). Again, if the risk assessment is missed, refused, or if risk is denied the workflow may terminate. The expectation is that when risk is confirmed, depending on acuity, a referral is made to outpatient supportive services or to the emergency department or inpatient setting.

The enhanced care suicide risk model (intervention) demonstrates the proposed changes in workflow with the risk model implementation. In this model, the suicide risk model flags the clinician in the EHR to conduct additional suicide risk screening. The expectation is that if the PHQ9 were missed, refused, or if item 9 was denied in the presence of a model-generated risk flag indicating elevated estimated risk, then the clinician would proceed to the C-SSRS as if the screening were positive.

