It is important to note that among patients who present for behavioral health services, some will have minimal or no suicide risk, some will be thought to be at *clinical* risk (i.e., the treating clinician estimates the patient is at risk) [44] but will not be flagged at *estimated statistical* risk by the risk model, some will be flagged at estimated statistical risk but will deny acute clinical risk (e.g., some may have enduring suicide ideation that is being treated), and some flagged at estimated statistical risk will be confirmed, upon assessment, to be at acute clinical risk (for some this will be an incident recognition, others will already be identified and perhaps treated). The goal of the model is to prompt risk assessment of anyone determined to be at estimated elevated statistical risk, and to prompt supportive preventive services when appropriate. How care proceeds after the risk assessment is dependent on the outcome of the risk assessment and the clinician’s judgement. This is an important detail because clinicians and patients have expressed concern about risk models having the potential to lead to coercive or inappropriate treatment; the risk model prompts identification and recognition of risk but is agnostic to treatment decisions thereafter.

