### Study measures and effectiveness outcomes

The primary outcome measure is fatal or non-fatal suicide attempt (binary yes/no) within 90 or 180 days of a behavioral health visit as measured using diagnosis codes for intentional self-harm (International Statistical Classification of Diseases and Related Health Problems, Tenth Revision [ICD-10] codes X60-X84; Y87.0). Suicide deaths will be ascertained from government mortality records. The denominator will be the total number of visits to behavioral health clinics and the numerator will be reported as the number of suicide attempts per 1000 visits. In addition to the primary outcome, we will examine proximal outcomes and crisis utilization measures. Proximal outcomes include measures of engagement with services documented in the EHR within the observation period. These are defined as: evidence-based suicide prevention interventions (safety planning, lethal means counseling, or caring contacts) on or after the risk identification (index) encounter, an outpatient encounter (includes telephone, virtual, and office visits) by a behavioral health clinician or psychiatrist subsequent to the index encounter, any contact with behavioral health within seven or 14 days of the index visit (includes phone calls, letters, patient portal messages, or other caring contacts in addition to encounters described above), frequency of contacts, latency to next encounter after index, and persistence in psychotherapy defined as no gap in psychotherapy visits > 90 days during the observation period. Crisis utilization measures include any encounters in the emergency department or inpatient stays subsequent to the index encounter within 90 days and 180 days.

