These models will also be used to test mediators/mechanisms, given that we hypothesize that identification alone will not reduce suicide outcomes but rather increase the number of people receiving suicide intervention, which could lead to improvement (i.e., decrease) in suicide outcomes. Mechanisms include interaction with the alert and initiation of assessment, which starts the outpatient care pathway. We will also stratify analyses by health system site, and test for mental health diagnoses and prior suicide attempts as moderators. Importantly, we will exclude ‘training’ months for each phase of clinic implementation from the main analyses, since clinicians and patients may be partially exposed as the models are implemented and clinicians trained. In a secondary set of analyses, we will explore potential heterogeneity in treatment effects between clinics. Here we will conduct additional analyses to test within cluster comparisons of exposed and unexposed periods.

To examine the effectiveness of a suicide risk model on health service engagement and suicide attempt outcomes, we will start with similar descriptive and GLMMs analyses proposed previously for identification and recognition. The analyses here will focus on each unique health service engagement (supportive and crisis encounters separately) and suicide attempt outcomes, stratified by exposed (intervention) versus unexposed (control) groups. Suicide attempts will be captured by health system records using ICD-10 diagnosis codes occurring within the same 90-day and 180-day time periods. We will also use a Kaplan-Meier method and Cox-proportional hazards models to examine time-to-event for health service engagement and suicide attempts, with statistical adjustment for clinical and demographic factors. Individuals will be censored at the time of death or at 180 days past the index visit. We will again add terms for calendar month as well as site to account for variation by season and health system.

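### The crisis-use total mixes referrals arising from the index assessment with later crises, so it can rise, or hide a fall in later crises, partly because the pathway works as intended

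*Protocol article*

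**What the plan says.** **Definition.** Under Study measures and effectiveness outcomes, the protocol article states: "Crisis utilization measures include any encounters in the emergency department or inpatient stays subsequent to the index encounter within 90 days and 180 days". The sentence sets no rule for encounters that arise from the index visit itself.

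**Direction of benefit.** Objectives and hypotheses asks of intervention-clinic patients: "Are they less likely to require crisis services and less likely to attempt suicide". The Background says earlier work did not test whether the models "result in patients receiving more suicide prevention services (treatment) and fewer crisis services or making fewer suicide attempts", and that this study is designed to answer that.

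**Pathway.** Under Proposed care models, when risk is confirmed, "depending on acuity, a referral is made to outpatient supportive services or to the emergency department or inpatient setting". For a flagged patient whose PHQ9 was missed or refused, or whose item 9 was denied, "then the clinician would proceed to the C-SSRS as if the screening were positive". The trial hypothesises that "suicide risk model implementation will improve identification and recognition of patients at increased risk of suicide attempt compared to usual care". The same section adds that "the risk model prompts identification and recognition of risk but is agnostic to treatment decisions thereafter".

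**Analysis.** The Analysis plan for effectiveness outcomes compares exposed with unexposed groups: "The analyses here will focus on each unique health service engagement (supportive and crisis encounters separately) and suicide attempt outcomes". It also plans mediation models with behavioral health engagement within 7 and 14 days as the mediator, and repeats them with crisis services as the outcome.

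**The concern.** An emergency visit or admission arranged from the index assessment has two roles in this plan. It is a possible step of the care pathway that the flag should trigger more often, and it is an event in an outcome where fewer means better. Nothing in the article separates it from an unplanned crisis weeks later.

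If recognition rises as hypothesised, some extra index-linked encounters can appear in the intervention periods. Two misreadings become possible: a rise in the total taken as harm when it reflects referral after assessment, and a real fall in later crises hidden inside a flat total.

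The mediation models add a problem of time order. An index-linked admission can occur before the 7- or 14-day engagement window closes, so the outcome can precede the mediator said to affect it.

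**Working it through.** **1. Is there a figure to reproduce?** No. The article gives no crisis-use rate, effect size or power. The structural point comes from setting the passages side by side: the flag leads to more assessments; confirmed risk leads, for some patients, to emergency or inpatient referral; the outcome counts emergency and inpatient encounters after the index visit; fewer is read as better.

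**2. Illustration among flagged patients.** All four inputs are assumptions:
- c: usual-care risk of a later crisis encounter
- d: true relative reduction in later crises
- q: extra share with risk confirmed because of the flag
- r: share of those referred to emergency or inpatient care

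Observed risk under intervention = c(1−d) + q·r·[1 − c(1−d)].

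Only the extra referrals are modelled. Referrals that would occur in usual care anyway are left out of both sides.

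**3. Worked examples.**
- *Reversal.* c = 10%, d = 10%, q = 40%, r = 5%: 0.09 + 0.02 × 0.91 = 0.1082. That is 10.8% against 10.0%, a ratio of 1.08 despite a true 10% reduction.
- *Masking.* c = 10%, d = 20%, q = 20%, r = 5%: 0.08 + 0.01 × 0.92 = 0.0892. That is 8.9% against 10.0%, so a true 20% reduction looks like about 11%.

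**4. Break-even.** Setting the observed risk equal to c gives q·r = c·d / [1 − c(1−d)].

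| c | d | q·r that cancels the benefit |
|---|---|---|
| 5% | 10% | 0.005/0.955 = 0.5% |
| 5% | 20% | 0.010/0.960 = 1.0% |
| 10% | 10% | 0.010/0.910 = 1.1% |
| 10% | 20% | 0.020/0.920 = 2.2% |
| 20% | 10% | 0.020/0.820 = 2.4% |
| 20% | 20% | 0.040/0.840 = 4.8% |

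**5. Range.** Over c = 5, 10, 20%; d = 10, 20%; q = 20, 40%; and r = 2, 5, 10% (36 combinations), the observed ratio runs from 0.82 to 1.66 and exceeds 1 in 13.

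**6. If the comparison covers all patients.** The article projects 4–5% of patients identified as high risk. If all effects fall on them, the 0.82-point net excess in the reversal example becomes 0.82 × 0.04 = 0.03 to 0.82 × 0.05 = 0.04 points. The true 1.0-point benefit shrinks by the same factor, to 0.04–0.05 points, so the sign is unchanged.

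**7. What the split shows.** In the reversal example the later component is 9.0% against 10.0%, which shows the benefit, and the extra referrals appear separately as 0.40 × 0.05 = 2.0% of flagged patients. This assumes that an early admission does not itself alter later crisis risk.

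**The case against.** **Total crisis use is a legitimate pragmatic outcome.** An admission prompted by the flag is a real effect of the intervention. The article itself reports concern about coercive or inappropriate treatment, and a total count would reveal it. This stands. A reader might infer that the crisis question cannot be answered as measured, but whether total use falls can be answered.

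**The pathway does not route all confirmed-risk patients to emergency or inpatient care.** A reader might infer that it does. The article says that referral depends on acuity, leaves care after assessment to the clinician, and describes the step within usual care. This stands too. What remains is narrower: the flag is meant to move more patients to a step where such referral is one possible result.

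**The measure need not contradict a stated hypothesis.** The explicit hypotheses concern suicide attempts, supportive services, identification and recognition. Crisis use is posed as a question. That is correct, but the direction of benefit is plain from that question and from the Background.

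**The all-encounter wording may be narrowed elsewhere.** Data sources refers to validated network definitions that are not shown. The absence of a diagnosis restriction is therefore not established as an error.

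**Same-day encounters may already be excluded.** The article counts prevention interventions on or after the index encounter but crisis use only after it. Whether a same-day transfer counts is unclear, which is a reason for a stated rule.

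**Kaplan-Meier and Cox analyses could show an early rise.** They could, but no rule says how to interpret one.

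**Replacing the total with a later-only outcome would bias the result.** Patients admitted early spend part of the later window in hospital. This stands and shapes the fix.

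**Conclusion.** The point holds as one of interpretation and pre-specification. The crisis total combines encounters that the pathway may generate at the index assessment with later crises that the trial hopes to reduce, and the article has no rule to tell them apart. The total can rise, or mask a fall in later crises, partly because the intervention works as intended.

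The size cannot be computed from the documents. On assumed values, extra referrals in 0.5% to 4.8% of flagged patients would cancel a true 10–20% reduction in later crises. Reversal is possible, not certain. It would be too strong to say that the measure is invalid or that it will show harm.

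The point touches the crisis-use comparison and the crisis mediation models, not the suicide-attempt primary outcome.

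**What to change.** 1. Keep the total emergency and inpatient count to 90 and 180 days as the net-effect measure, and state whether it includes encounters on the index date.
2. Pre-specify a split by one calendar-time rule, identical in baseline and intervention periods: *index-linked* encounters, starting on the index date or within a fixed short window (for instance 2 days), and *later crises*, starting after that window to 90 and 180 days. Classify by time, not by recorded referral, so that the rule does not depend on how referrals are documented in each period.
3. Report all three by exposure period, and answer the crisis-services question from the total and the later component together.
4. In the crisis mediation models, count only encounters that start after the 7- or 14-day engagement window, so that the outcome does not precede the mediator.
5. If the cited definitions do not already restrict the measure, add a version limited to behavioral health or self-harm diagnoses as a sensitivity analysis.

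**Cost.** A change of outcome wording and a little more analysis. Encounters and diagnoses are already captured in the data warehouse. The later component is affected by time in hospital after early admissions, so it must be read with the total and must not replace it. The change concerns measurement only, not clinical management.

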Secondary outcomes include suicide risk identification and recognition. Identification will be measured by the number and proportion of patients estimated to be at elevated risk by PHQ9 item 9, the risk model, or both, stratified by race/ethnicity. This will be assessed at each visit, as multiple visits may occur for the same individual. However, when calculating identification and recognition, we will aggregate visits at the individual level—categorizing outcomes as yes/no for binary measures and recording the number of identifications and recognitions as count outcomes. Aggregated assessment results will be generated at 90 and 180 days. Therefore, the denominator is the number of unique patients with an encounter in the study period. In the intervention clinics we will also measure the number of patients flagged by the risk model who, at the index encounter, did not complete the PHQ9 or denied item 9. Those identified by the risk flag but not through traditional PHQ-9 will represent the gain from using a model-based identification approach; in the usual care model these patients would not be identified as having elevated estimated increased risk. Suicide risk recognition will be measured by the number and proportion of patients who complete a risk assessment (C-SSRS), stratified by race/ethnicity, where the denominator is the number of unique patients with an encounter in the study period. We will also measure the proportion who completed a C-SSRS but did not have an elevated PHQ9 item 9 score but were estimated to be at elevated risk by the suicide risk model (for comparison, this will also be measured among usual care control participants as some patients will receive risk assessments independent of prompting by PHQ9 item 9 score).

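### The count labelled as the gain from the risk model (patients flagged without a positive PHQ9 item 9 at the index visit) is only an upper bound on the gain over usual care

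*Protocol article*

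**What the plan says.** Under Objectives and hypotheses, the article asks: "does the risk model (intervention) identify additional patients for screening who would not be identified in the course of usual care". Under Study measures and effectiveness outcomes it sets out a count for the intervention clinics, namely the patients "flagged by the risk model who, at the index encounter, did not complete the PHQ9 or denied item 9". It then interprets that count: "Those identified by the risk flag but not through traditional PHQ-9 will represent the gain from using a model-based identification approach". The justification follows at once: "in the usual care model these patients would not be identified as having elevated estimated increased risk".

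Other statements bear on that justification. Under Proposed care models, the article describes flagged patients who are confirmed on assessment to be at acute clinical risk: "for some this will be an incident recognition, others will already be identified and perhaps treated". Of flagged patients who deny acute clinical risk, it says "some may have enduring suicide ideation that is being treated". For usual care after a missed, refused or denied item 9, it says "the workflow may terminate, however a clinician could also proceed if clinically indicated". In the recognition measure, it expects of usual-care controls that "some patients will receive risk assessments independent of prompting by PHQ9 item 9 score".

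**The concern.** The counterfactual is stated without qualification, but the article gives reasons to think that it fails for some of the patients counted. A patient who is under treatment for long-standing ideation and denies item 9 today is flagged, is negative on the PHQ9 at the index visit, and so falls inside the gain. Nothing in the definition removes a patient with an earlier positive item 9, an earlier positive C-SSRS, a safety plan or a coded self-harm event.

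What is at stake is the description of what the model adds. The trial's findings are to be summarised in a tool kit for health care leaders who are considering adoption. Those leaders would read a figure called the gain as patients their clinics would otherwise have missed.

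**Working it through.** The article gives no figure for the gain, so there is nothing to reproduce. The check sets the statements side by side and then works out what can be said about size.

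**Step 1. What the question covers.** The objective concerns patients not identified in the course of usual care. That is wider than one questionnaire item at one visit.

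**Step 2. What the count covers.** It contains flagged patients not found through the PHQ-9, with PHQ9 status read at the index encounter. General identification results are aggregated per patient at 90 and 180 days, but this count is tied to one visit. A patient positive on item 9 at another visit could therefore still be in it.

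**Step 3. Whom the count includes but the question excludes.**

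| Statement in the article | Bearing on the count |
|---|---|
| Some flagged patients who deny acute risk have ideation under treatment | Direct: such patients can deny item 9 and be counted |
| Some flagged patients confirmed at acute risk are already identified or treated | Direct where item 9 was missed, refused or denied at the index visit |
| Usual-care clinicians may proceed without a positive item 9 | Indirect: a usual-care route to assessment, not to screening |
| Some controls get a risk assessment without an item 9 prompt | Indirect: same route, and measured under recognition only |

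**Step 4. Direction.** Let G be the reported count and s the share of it already identified or treated. The net gain is G × (1 − s), and the overstatement factor is G / [G × (1 − s)] = 1 / (1 − s). For any s above zero the factor exceeds 1, so these patients can only push the count upward.

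**Step 5. Size.** The article does not give s. With assumed values:

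- s = 10%: 1 / 0.90 = 1.11
- s = 25%: 1 / 0.75 = 1.33
- s = 50%: 1 / 0.50 = 2.00

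G cannot be derived either. Sample size and power analysis projects that 4–5% of 395,000 patients will be high risk: 0.04 × 395,000 = 15,800 and 0.05 × 395,000 = 19,750. That is a projection for all patients over 2.5 years. The count is restricted to intervention clinics and leaves out item-9-positive patients, so these figures are not its base.

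**The case against.** The article separates identification (screening) from recognition (risk assessment), and the gain statement is about identification. A C-SSRS started on clinical judgement is recognition and is counted there. This stands: the last two rows of the table do not contradict a statement about screening. It would go too far to say that the article refutes itself on three separate counts.

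The article also contrasts clinical risk with estimated statistical risk. If estimated risk in the gain sentence means model-estimated risk only, the sentence is true by definition, because the usual-care workflow has no model. This reading is available. On it, however, the count says nothing about patients whom usual care would miss, which is what the objective asks and what the word gain conveys.

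Comparisons with usual care are planned. C-SSRS completion without an elevated item 9 among patients at elevated model risk is also to be measured in controls, and mixed models compare exposed with unexposed periods. The control measure is a real partial mitigation. Neither comparison changes the composition of the gain count. The rule that unique patients have had no visit in the past three months is a visit gap, not a check for recorded risk, and it is not applied to this count.

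Detailed look-back rules can be left to an analysis plan. Here, though, the article itself fixes both the label and the counterfactual.

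A reader might infer that most flagged patients are already known, because the model draws on health records and claims. The article neither lists the predictors nor gives that share, so this is not supported.

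**Conclusion.** The concern holds as a matter of labelling and interpretation. As an answer to the article's own question, the count is an upper bound on the patients gained. This assumes that the gain covers every flagged patient without a positive item 9. The article treats scores of 2 or 3 as positive but counts patients who denied the item or did not complete it, so the handling of a score of 1 is not explicit.

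The overstatement is established in direction only. The factors of 1.11 to 2.00 rest on assumed shares and are not estimates for this trial. A reader might take 15,800–19,750 as the gain, or infer that the effect on suicide attempts is biased. Neither follows: the first is the wrong base, and the primary outcome, the power statement and the model-based comparisons do not use this count.

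**What to change.** 1. Report the count under a neutral name: flagged without positive item 9 at index. Delete or qualify the sentence saying that usual care would not identify these patients.

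2. Split the count with a fixed look-back that ends before the patient's first flag, so that a C-SSRS prompted by the flag is not read as prior knowledge. One group has positive evidence of recognised risk on record: a positive item 9, a C-SSRS with a positive result, a safety plan or lethal-means counseling, or a self-harm code. The other has none. A negative C-SSRS must not count as already known. C-SSRS use is established at participating sites, and counting any C-SSRS would wrongly move patients who screened negative out of the gain.

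3. Call only the second group the gain and show both groups. Read them beside the planned control-period measure of C-SSRS completion without an elevated item 9. A look-back cannot show whom a clinician would have assessed at that visit anyway.

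The cost is wording, one derived variable from the health-record and data-warehouse sources already in use, and a smaller reported gain. Past-year attempt is already among the planned descriptive variables. Patients with an old record who conceal risk today would leave the gain, which is why both groups should be shown.
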